#### **Dose and Mode of Administration:**

Each day of the Experimental test period (6 weeks or 42 days) 0.8 mL (one pump) of the product is applied to the varicose vein and surrounding area twice a day. This dosage is in alignment with the products licensed use.

#### **Product and Ingredients' List:**

The "LivRelief- Varicose Vein Cream" is being used for this study:

- NPN#: 80029345.
- List of ingredients:
  - **Active Ingredient:** Hamamelis virginiana L. (Witch Hazel) bark 10%

- **Non-Medicinal Ingredients:** Aesculus Hippocastanum (Horse Chestnut) Seed Extract, Arnica Montana Flower Extract, Black currant seed oil, Butylene Glycol, Carnauba Wax, Cetearyl olivate, Cetyl Palmitate, Chlorphenesin, Citrus limon extract, Dicaprylyl carbonate, Ethoxydiglycol, Glycerin, Goldenrod extract, Lecithin, Peucedanum ostruthium Leaf extract, Polyacrylate-13, Polyisobutene, Polysorbate 20, Purified water, Rosemary extract, Rubus idaeus (Raspberry) Seed oil, Ruscus Aculeatus Root Extract, Rutin, Sambucus nigra flower extract, Sorbitan Palmitate, Sorbitan olivate, Sunflower oil, Xanthan Gum, sodium phytate

### **Definition of endpoints:**

#### *Primary:*

- Collection of data and completeness of datasets.

#### *Exploratory analysis:*

- Evaluation of statistical differences (if any) in objective and/or subjective measures at onset and completion of the trial.

### **Measurements and measurement instruments:**

A combination of Objective and Subjective methods will be employed in this interventional study.

#### *Objective measures:*

- Circumferential measurements of the limb will be collected at onset and completion (twice) of the trial.  
Three landmarks will be used on the leg:
  - Mid foot
  - 5 cm proximal to the medial malleolus
  - 5 cm distal from the tibial tuberosity
- Photographic evidence of the discoloration of the skin in the vicinity of the varicose vein/limb along with incremental (metric) measure in frame. Photographic information will be collected at onset and completion (twice) of the trial.

#### *Subjective measures:*

- Clinical grade, Etiology, Anatomy, and Pathophysiology (CEAP) classification of the varicosity. The CEAP classification is assessed at onset and completion (twice) of the trial.
- Quality of Life Enjoyment and Satisfaction Questionnaire – Short Form (Q-LES-Q-SF) is recorded as Quality of Life questionnaire. The Q-LES-Q-SF is administered at onset and completion (twice) of the trial.

A Phase IV Interventional Pilot study of a licensed topical product for the treatment of varicose  
veins in adults  
Protocol V4 – May 2017

- Venous Clinical Severity Score (VCSS). The VCSS is assessed at onset and completion (twice) of the trial.
- Adverse events collection as self-reported incidents at the completion of trial and specific inquiries in regards to any adverse events at the site of administration, including rashes.

### Schedule of Assessments

As described in Table 2, on Day 1 of the study the participant completes the Informed Consent Form (ICF), is evaluated according to inclusion and exclusion criteria, undergoes CEAP classification of the region in question, photographed within and limited to the region in question, limb diameter measurement, and Q-LES-Q-SF in this chronological order. On the same day and subsequent to these evaluations and measures the product is applied for the first time (Day 1) and materials and instructions are provided for self-administration over the proceeding period (41 days).

At the end of six weeks (42 days +/- 3 days) the same schedule of assessments is administered (with the exception of consent, pregnancy test and inclusion/exclusion) as well as self-reported adverse events, if any.

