**Study purpose and rational:**

LivRelief Varicose Vein Cream is a Natural Health Product licensed as a treatment for venous stasis (NPN 80029345). This phase IV interventional pilot study aims to collect information on specific objective and subjective measures by the sponsor. Quality of Life is measured through the Quality of Life Enjoyment and Satisfaction Questionnaire – Short Form (Q-LES-Q-SF). In combination and complementary to this questionnaire, the Venous Clinical Severity Score (VCSS) is employed whose construction was targeted directly at repeat longitudinal evaluations. A preliminary dataset (N=30) is proposed in order to evaluate product use and data collection quality.

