#### **Study Design and Methodology:**

The present study is designed as a phase IV interventional pilot study.

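### Protocol V4 places the Q-LES-Q-SF after the leg examination at both visits, so Day 42 answers could be influenced by the repeat examination; moving it first is a minor, nearly free improvement

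*Supplement*

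**What the plan says.** The supplement holds Protocol V3 (April 2017) and V4 (May 2017); V4 is the version reviewed.

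- **Day 1 order.** Under Schedule of Assessments, after consent and the eligibility check, the participant "undergoes CEAP classification of the region in question, photographed within and limited to the region in question", followed by "limb diameter measurement, and Q-LES-Q-SF in this chronological order". The text presents this as a sequence in time.
- **End visit.** At six weeks, "the same schedule of assessments is administered (with the exception of consent, pregnancy test and inclusion/exclusion" are the terms; self-reported adverse events are added.
- **Table 2.** The rows run circumference, photograph, CEAP, Q-LES-Q-SF, VCSS. The three leg procedures are in a different order from the text, but the questionnaire again comes after all of them.
- **Timing of the questionnaire.** Subjective measures: "The Q-LES-Q-SF is administered at onset and completion (twice) of the trial".
- **Use in the analysis.** The exploratory analysis is "Evaluation of statistical differences (if any) in objective and/or subjective measures at onset and completion of the trial". The primary endpoint is "Collection of data and completeness of datasets".
- **Design.** "The present study is designed as a phase IV interventional pilot study". V4 describes no control arm, randomisation or blinding.

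**The concern.** The Q-LES-Q-SF is the only efficacy questionnaire that the participant completes (adverse events are self-reported too, but they are not an efficacy measure). It is taken last in the stated sequence, after staff have examined the leg.

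The same order applies at both visits, but that protects the change score only against an order effect of equal size at each visit. At Day 1 there is no earlier reading to compare with. At Day 42 the participant has just been through a second grading, photograph and tape measurement, after six weeks of knowingly using the product. A remark by staff, or the participant's own impression of the repeat examination, can enter the answers at that visit only. It would then be counted as change in quality of life, and with one arm nothing in the design could reveal or offset it.

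At stake is how one exploratory comparison is read. The feasibility conclusions are not at stake.

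**Working it through.** The plan gives no figure on this point, so there is none to reproduce. The check is mainly a reading of the text, with one illustrative calculation.

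**Step 1. Is the order fixed?** For Day 1, yes: the text calls the sequence chronological and puts the Q-LES-Q-SF last. For the end visit it is inferred from the statement that the same schedule applies. That is the natural reading, but it is not a separate explicit rule.

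**Step 2. Does Table 2 agree?** On the position of the questionnaire relative to CEAP, photograph and circumference, yes. Its rows differ from the text in other respects, so they may not be meant as a sequence, and the table is only weak support.

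**Step 3. Which assessments precede the questionnaire?** CEAP, photograph and limb measurement. VCSS is absent from the ordered list in the text and follows the Q-LES-Q-SF in Table 2. Any statement that the leg has been graded first therefore rests on CEAP alone.

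**Step 4. Does anything in V4 block the influence?** V4 neither requires the questionnaire first nor says that findings are withheld until it is complete. It also does not say that findings are disclosed.

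**Step 5. What cancels and what does not?** Let *b* be an order effect common to both visits and *f* a reaction to the repeat examination at Day 42. With true change Δ, the expected observed change is (Δ + *b* + *f*) − *b* = Δ + *f*. The common part drops out; *f* remains, and a single arm cannot separate it from Δ.

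**Step 6. Illustration only.** Inputs from the documents: N = 30 ("A preliminary dataset (N=30) is proposed in order to evaluate product use and data collection quality"), and 0.70 × 30 = 21 if completeness just meets the 70% criterion. Inputs assumed here: a paired t-test at two-sided 5% (V4 names neither test nor level), Δ = 0, and *f* = 0.1, 0.2 or 0.3 SD of the change. The test statistic is noncentral t with *n* − 1 degrees of freedom and noncentrality λ = (*f*/SD) × √*n*. The chance of significance is P(|T| > t₀.₉₇₅).

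| Assumed shift *f* (SD of change) | n = 30: λ | n = 30: P(significant) | n = 21: λ | n = 21: P(significant) |
|---|---|---|---|---|
| 0 | 0 | 5% | 0 | 5% |
| 0.1 | 0.55 | 8.3% | 0.46 | 7.2% |
| 0.2 | 1.10 | 18.5% | 0.92 | 14.1% |
| 0.3 | 1.64 | 35.5% | 1.37 | 25.8% |

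The test is two-sided, so a negative *f* of the same size gives the same probabilities, pointing towards apparent worsening. The table shows how sensitive a sample of this size would be to a shift if one existed. It is not evidence that one exists.

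**The case against.** The strongest reply is that the feedback is assumed. V4 lists what is collected at Visit 2; it does not say that Day 1 readings or photographs are shown to the participant, and seeing a tape measure does not tell someone what has changed since six weeks before. **This stands.** A reader might infer that participants are told whether the leg has improved, or that the Q-LES-Q-SF result will be biased upwards. The documents support neither. Disclosure is merely not excluded, and disappointing feedback would lower scores. If the leg has not changed, accurate feedback need not produce any net shift.

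Second, participants apply the cream to the visible vein twice a day and know that they are treated. They arrive with an opinion already formed. By Table 2 the three leg procedures take at most 5 + 2 + 5 = 12 minutes, so moving the questionnaire removes only what those minutes add. **This also stands**, and it limits what the change can achieve.

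Third, the outcome is exploratory in a feasibility pilot. **This stands as to weight.** It does not remove the point, because V4 gives data collection quality as a purpose of the 30-participant dataset, and the order in which a self-report is taken belongs to that.

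Fourth, CEAP is the eligibility screen, so doing it first on Day 1 avoids questionnaires from people who turn out to be ineligible. **This is a fair reason for the Day 1 order**, but it is worth only 2 minutes per ineligible person and does not apply at Visit 2.

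**Conclusion.** The point holds as a minor one. V4 places the Q-LES-Q-SF after CEAP, photograph and limb measurement on Day 1 and, on the natural reading, at the end visit too. Nothing in V4 guards the Day 42 answers against influence from the repeat examination. Any such influence would pass uncancelled into the exploratory onset-to-completion comparison.

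The conclusion rests on two things: reading the end-visit schedule as keeping the Day 1 order, and V4's silence on withholding findings. Neither the size nor the direction of an effect can be derived from the documents, and the 0.1 to 0.3 SD range is illustrative only. It would be wrong to read the point as showing that the quality-of-life comparison is biased, or as touching the primary endpoint or either 70% feasibility criterion.

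**What to change.** In Schedule of Assessments and Table 2, have the participant complete the Q-LES-Q-SF before any leg assessment (CEAP, VCSS, photograph, circumference) at both visits:

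- **Visit 1:** after consent and those eligibility questions that need no examination.
- **Visit 2:** on arrival, before any discussion of findings from either visit.

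State the order for Visit 2 explicitly, include VCSS in the ordered list, and make the text and the table rows agree.

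The cost is a reworded sentence or two, re-ordered table rows and the matching case report form pages, with no added staff or visit time. The one downside is an occasional 2-minute questionnaire from a participant who then fails the CEAP screen.

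The change closes one avoidable route of influence. The comparison remains uncontrolled, so a pre-post difference in Q-LES-Q-SF would still not be attributable to the cream.

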**Table 2 Graphical Schedule of Assessments**

| EVENT (maximum duration)                                                              | Screening and Baseline
Visit 1
(Day 1) | Experimental
Period
(Day 2-40) | End Visit
Visit 2
(Day 42) |
|----------------------------------------------------------------------------------------------|-------------------------------------------------------|-----------------------------------------------|-------------------------------------------|
| Informed Consent Form (2 minutes)                                                            | ✓                                                     |                                               |                                           |
| *Pregnancy Test (5 minutes)                                                                  | ✓                                                     |                                               |                                           |
| Inclusion/Exclusion Criteria Evaluation (2 minutes)                                          | ✓                                                     |                                               |                                           |
| Leg Circumferential measurement (5 minutes)                                                  | ✓                                                     |                                               | ✓                                         |
| Skin Discoloration assessment (photography) (2 minutes)                                      | ✓                                                     |                                               | ✓                                         |
| CEAP Classification (5 minutes)                                                              | ✓                                                     |                                               | ✓                                         |
| Quality of Life Enjoyment and Satisfaction
Questionnaire – Short (Q-LES-Q-SF) (2 minutes) | ✓                                                     |                                               | ✓                                         |
| Venous Clinical Severity Score (VCSS) (3 minutes)                                            | ✓                                                     |                                               | ✓                                         |
| Cream Application (twice a day) (<1 minute)                                                  | ✓                                                     | ✓                                             |                                           |

A Phase IV Interventional Pilot study of a licensed topical product for the treatment of varicose  
veins in adults  
Protocol V4 – May 2017

|                           |   |   |   |
|---------------------------|---|---|---|
| Adverse Events Evaluation | ✓ | ✓ | ✓ |
|---------------------------|---|---|---|

**\*A pregnancy test is not required for female subjects of “non-childbearing potential”, i.e.: sterile or post-menopausal. Female subjects will state their reproductive status at screening.**

